## Abstract

**Background**: The number of older patients undergoing cardiac surgery is increasing, and a substantial proportion of these patients are frail. Frailty is associated with increased mortality, psychological complications, functional decline, and reduced health-related quality of life, complicating treatment decision-making. Currently, treatment recommendations are formulated by the multidisciplinary Heart Team and are mainly based on disease-related parameters. To better integrate patient preferences, geriatric assessment, and shared decision-making into routine cardiothoracic practice, a nurse-led preoperative outpatient pathway was developed: the Preoperative RIsk assessment and shared decision-Making in patients Eligible for cardiac surgery (PRIME) clinic. This study aims to evaluate whether the implementation of PRIME consultation influences Heart Team treatment recommendations and to assess its cost-effectiveness. **Methods**: This single-center, non-randomized prospective study is conducted in the Netherlands. Patients aged ≥70 years who are eligible for cardiac surgery and have two or more risk factors for adverse postoperative outcomes are included. All patients are initially discussed in the Heart Team, resulting in a treatment recommendation. Patients in the intervention group subsequently visit the PRIME clinic, where a comprehensive geriatric assessment and a shared decision-making consultation are performed. Following this visit, patients are re-evaluated by the Heart Team. The primary outcome is the comparison between the initial and subsequent Heart Team treatment recommendations. Secondary outcomes include health-related quality of life and cost-effectiveness. **Discussion**: This prospective exploratory study evaluates the implementation of a novel, patient-centered preoperative care model integrating geriatric assessment and shared decision-making into routine cardiac surgical practice. By focusing on outcomes meaningful to older patients and their relatives, the study contributes to the development of value-based, individualized surgical care. **Trial registration**: The PRIME study was registered in ClinicalTrials.gov (trial registration number: NCT06616129).

## 1. Introduction

The number of older people requiring cardiac surgical interventions is increasing, and a substantial proportion of these individuals are frail [1,2]. Frailty is a syndrome characterized by reduced physiological reserves and impaired ability to maintain internal stability, leading to increased sensitivity to stressors, elevating the risk of adverse health outcomes [3]. Frail patients undergoing cardiac surgery face a significantly higher risk of mortality, prolonged institutional care, and deterioration in health-related quality of life [4]. In addition to surgery-related risks, hospitalization itself may negatively affect older patients, often leading to reduced mobility, loss of muscle strength, and progression of frailty [5]. Furthermore, the impact of cardiac surgery is not limited to cardiovascular factors; it also extends to psychological and emotional dimensions for both patients and their relatives [6,7]. Not only patients, but also relatives face a potentially life-threatening condition. Together, these factors contribute to the complexity and multifaceted nature of determining the optimal treatment plan. While clinical assessment of comorbidities and frailty is essential, patients’ preferences, expectations, and perceptions of health and quality of life should also be considered in treatment decision-making [8].

There is increasing awareness of the benefits of preoperative screening for cardiac surgical decision-making, especially in frail patients [8]. In addition, shared decision-making has been shown to reduce decisional conflict and anxiety, and may influence treatment choices [9,10]. Studies in non-cardiac surgical patients suggest that increased consideration of frailty tends to lead to less invasive treatment [11,12]. However, in the Netherlands, systematic assessment of frailty and patient preferences has not yet been widely implemented in routine cardiac surgical practice. This is likely due to concerns regarding time and resource requirements, as well as uncertainty about how to integrate shared decision-making into standard care [10]. As a result, treatment decisions made during Heart Team meetings, multidisciplinary discussions involving cardiothoracic surgeons and cardiologists, are primarily based on disease parameters.

Given the increasing number of frail older patients who are vulnerable to loss of life and independence, there is a compelling need to organize personalized care for this particular group. Therefore, a recently established outpatient clinic, the Preoperative RIsk assessment and shared decision-Making in patients Eligible for cardiac surgery clinic (PRIME outpatient clinic), was established. This nurse-led PRIME clinic facilitates structured conversations with patients and their relatives, incorporating a comprehensive geriatric assessment and shared decision-making approach to better align treatment decisions with patients’ preferences, expectations, and overall risk profile.

However, the impact of such an approach on treatment decisions and patient outcomes has not yet been formally evaluated. Therefore, the aim of this study is to determine the influence of the PRIME intervention on treatment recommendations made by the Heart Team. Secondary aims are to assess health-related quality of life in patients eligible for cardiac surgery and to evaluate the cost-effectiveness of the PRIME outpatient clinic.

## 2. Materials and Methods

### 2.1. Study Design

This is a single-center, non-randomized, exploratory, prospective trial with data collected during the cardiac treatment decision-making process and a one-year follow-up. Treatment recommendations provided during the first Heart Team meeting (prior to the patient’s visit to the PRIME clinic) will be compared with the (possibly revised) treatment recommendations from the second Heart Team meeting (after the patient’s visit to the PRIME clinic). In addition, patients’ health-related quality of life (measured by RAND-36 [13]) will be assessed at baseline and one year after their visit to the outpatient clinic. These data will be compared with those of a control group with a comparable risk profile who received standard care and did not attend the PRIME clinic.

To evaluate the cost-effectiveness in terms of quality-adjusted life years (QALYs), the EQ-5D-5L [14] and the Medical Consumption Questionnaire [15] (MCQ) will be administered quarterly over a one-year period. This study will be conducted in accordance with the SPIRIT (Standard Protocol Items: Recommendations for Interventional Trials) 2013 statement [16], at the University Medical Center Groningen (UMCG), the Netherlands. The trial is registered at ClinicalTrials.gov, with registration number NCT06616129.

Figure 1 provides the data collection timeline for the PRIME study design. The Template for Intervention Description and Replication checklist and guide was used to describe the PRIME clinic intervention [17].

### 2.2. Ethics Approval and Informed Consent

The study protocol was approved by the local Medical Ethics Committee (METc number 2022/006) on 10 January 2022 and was deemed not to fall under the scope of the Medical Research Involving Human Subjects Act [18] (WMO).

Written informed consent for participation in the study is obtained from all participants prior to participation. Following enrollment, a unique study identifier is assigned to each participant to ensure confidentiality and data anonymization.

### 2.3. Study Population

One of the major Dutch university heart centers is located at the UMCG, a tertiary referral center [19]. Within the UMCG, referred patients are discussed daily in the Heart Team, which consists of clinical and interventional cardiologists as well as cardiothoracic surgeons. During these meetings, the most appropriate treatment strategy for each patient is determined based on the information provided by the referring cardiologist, including comorbidities and diagnostic test results (e.g., coronary angiography, electrocardiography, and echocardiography).

Patients discussed in the Heart Team will be assessed for eligibility to participate in the PRIME study based on predefined inclusion and exclusion criteria. The inclusion criteria are: age ≥ 70 years, eligibility for cardiac surgery, and having two or more risk factors (see Table 1) associated with adverse outcomes following surgery. These preoperative risk factors include stroke, reduced cognitive function, chronic obstructive pulmonary disease (COPD), obesity, reduced left ventricular ejection fraction, renal failure, reduced mobility, cardiac reoperation, and procedural complexity. The selection of patients with ≥2 risk factors was based on clinical experience and evidence indicating that the accumulation of multiple risk factors is associated with increased postoperative risk in older cardiac surgery patients [20,21,22]. This approach aims to identify a population at higher risk of adverse outcomes, in whom a comprehensive geriatric assessment and shared decision-making are most likely to be clinically relevant.

The control group will consist of elective cardiac patients who received standard care without PRIME consultation. Control patients will be selected from an historical institutional database. To assess whether a tailored treatment plan following PRIME consultation affects health-related quality of life, a control group of approximately 70 control patients will be selected using nearest-neighbor matching. Matching will be based on baseline physical health-related quality of life (RAND-36) and surgical risk as estimated by the EuroSCORE II, to ensure comparable baseline risk profiles and potential for improvement in health-related quality of life [22]. Patients who are unable to read or understand Dutch will be excluded from participation.

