### 2.8. Outcomes and Measures

Demographic variables include age at the time of the PRIME clinic visit, or at the time of referral to the Heart Team in the control group, as well as sex. Social status at inclusion will be categorized as ‘married or living with a partner’ or ‘unmarried, divorced, or widowed. Education level will be classified according to the Dutch system described by Verhage and the Dutch Central Bureau of Statistics [32], categorizing education into low, medium, and high levels. Relevant comorbidities will be extracted from electronic medical records.

The primary outcome is the difference between the treatment recommendation provided by the multidisciplinary Heart Team prior to the patient’s visit to the PRIME clinic and the recommendation after the PRIME consultation. A revised treatment recommendation is defined as a reconsideration of the initially proposed open-heart surgery discussed during the first Heart Team meeting. In such cases, a less invasive or conservative treatment may be recommended instead of open-heart surgery.

Health-related quality of life will be assessed using the RAND-36 questionnaire [13] in both the intervention and control groups. Measurements will be performed at baseline (prior to the PRIME clinic visit, or 1–4 weeks before surgery in the control group) and at one-year follow-up. The RAND-36 is a validated self-administered questionnaire equivalent to the Short Form-36 (SF-36) for assessing health-related quality of life. It consists of 36 items that evaluate eight health dimensions: physical functioning; role limitations due to physical health; role limitations due to emotional problems; social functioning; emotional well-being; energy levels and fatigue; pain; and general health perceptions [13]. Scores range from 0 to 100, with higher scores indicating better health. Two composite scores can be derived from these domains: a Physical Component Score and a Mental Component Score.

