## 3. Discussion

The PRIME study will be the first prospective trial to compare cardiac treatment recommendations provided by a multidisciplinary Heart Team before and after a geriatric assessment combined with a structured shared decision-making conversation. In addition, the study will provide insights into patients’ health-related quality of life before and one year after the PRIME consultation and will compare these outcomes with those of a similar group of patients who did not undergo a PRIME consultation. Furthermore, the cost-effectiveness of the PRIME clinic will be evaluated. While the primary goals of cardiac surgery are to improve survival and enhance quality of life [37], previous studies have shown that not all patients benefit from cardiac surgery in terms of improved quality of life [38,39]. Older patients in particular may be at a higher risk of a decline in quality of life and reduced independence following surgery.

Currently, most patients scheduled for cardiac surgery are only seen by healthcare professionals from the cardiothoracic department shortly before surgery. This may lead to late reconsideration of vitality status or operability, requiring valuable time from healthcare providers and causing stress for both patients and their relatives. A key strength of this study is that the implementation of the PRIME clinic enables earlier identification of patient-specific risks and preferences. By integrating this information into the decision-making process, treatment decisions may become more timely and better aligned with patient values, contributing to a more patient-centered approach.

An additional advantage of the PRIME clinic may be the active role of nurses and nurse practitioners in the decision-making process. Despite the recognition of the significance of their role, cardiothoracic nurses and nurse practitioners are currently not involved in the treatment decision-making process, even though they are adequately trained and well-positioned to engage in shared decision-making with patients [40,41].

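### Historical controls are matched on two variables, without the PRIME entry criteria being stated for them and with a baseline tied to upcoming surgery, so the secondary RAND-36 comparison is open to selection and time-zero bias.

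*Protocol article*

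**What the plan says.** All places are in the protocol article.

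- **Who the controls are (2.3):** "The control group will consist of elective cardiac patients who received standard care without PRIME consultation". On their source: "Control patients will be selected from an historical institutional database".
- **How they are chosen (2.3):** "a control group of approximately 70 control patients will be selected using nearest-neighbor matching". The variables follow: "Matching will be based on baseline physical health-related quality of life (RAND-36) and surgical risk as estimated by the EuroSCORE II". The same sentence says that this is done to ensure comparable baseline risk and comparable room for improvement.
- **Who the PRIME patients are (2.3):** age 70 or over, plus "eligibility for cardiac surgery, and having two or more risk factors" from Table 1.
- **What comparability is promised (2.1):** a "control group with a comparable risk profile who received standard care and did not attend the PRIME clinic". Section 2.10 repeats the idea of a comparable risk profile and adds no further definition.
- **When RAND-36 is measured (2.8):** at "baseline (prior to the PRIME clinic visit, or 1–4 weeks before surgery in the control group) and at one-year follow-up". For PRIME patients, 2.1 counts the year from the clinic visit. For controls, no starting point for the year is given.
- **How it is analysed (2.10):** control scores are compared with PRIME scores. No test or adjustment is named for this contrast.

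**The concern.** Section 2.3 gives this comparison a causal purpose: to learn whether a tailored plan after PRIME changes quality of life. Section 3 then treats evidence of a quality-of-life benefit as something to weigh before larger studies. The result will be read as an effect, so the two groups should differ only in PRIME exposure.

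As written, they may differ in two other ways. PRIME patients pass an age and risk-factor screen that is not stated for controls. Controls are observed from a point defined by their coming operation, while PRIME patients are observed from before the final decision. Both differences could make controls look better at one year without any effect of PRIME. The study could then report no benefit, or harm, for reasons of selection.

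**Working it through.** **1. The plan's own figures.** The only size calculation is for the primary outcome (McNemar, 20% changing in one direction, none in reverse, two-sided 0.05, 90% power):

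n = [1.960 × √0.20 + 1.282 × √(0.20 − 0.04)]² / 0.20² = 48.24, rounded up to 49.

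The target of 70 equals 49 / 0.70. These figures reproduce, but they do not concern the RAND-36 control comparison, for which no power is stated.

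**2. Eligibility, side by side.**

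| | PRIME | Control |
|---|---|---|
| Age 70 or over | required | not stated |
| At least two Table 1 factors | required | not stated |
| Physical RAND-36, EuroSCORE II | as observed | matched |
| Period | prospective | historical |

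Two patients can have the same total on a composite score, and the same physical RAND-36, with different ages and different risk factors behind them. Matching on the two totals narrows the differences but does not ensure that they are gone.

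**3. Time zero, side by side.** PRIME baseline precedes the clinic visit, and so precedes the second Heart Team meeting. Control baseline is counted back from surgery. A patient under usual care who died, withdrew or was turned down before that window cannot be a control. Section 3 says that usual care sees patients only shortly before surgery and adds: "This may lead to late reconsideration of vitality status or operability". Matching on variables measured at baseline cannot undo selection on having reached that baseline. Section 2.8 also gives controls two index dates: age is taken at Heart Team referral, RAND-36 at 1–4 weeks before surgery.

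**4. Regression to the mean (conditional).** Let m be the matched baseline score, averaging the PRIME mean; μc the control pool mean; and rho the correlation between baseline and one-year scores. With no true effect and equal SDs:

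expected control score at one year = μc + rho × (m − μc) = m + (1 − rho) × (μc − m).

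On average, matched controls therefore drift up relative to PRIME patients by (1 − rho) × gap. The documents give neither the gap nor rho, so all inputs below are assumptions.

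| Gap (SD) | rho | Drift (SD) |
|---|---|---|
| 0 | any | 0 |
| 0.3 | 0.7 | 0.3 × 0.3 = 0.09 |
| 0.5 | 0.5 | 0.5 × 0.5 = 0.25 |
| 0.8 | 0.5 | 0.5 × 0.8 = 0.40 |

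A second set of assumptions (gap 5–15 points, rho 0.7–0.9, SD 20) gives 0.1 × 5 = 0.5 to 0.3 × 15 = 4.5 points, or about 0.03–0.23 SD. A simulation of nearest-neighbor matching on the score alone (70 PRIME patients, pool of 1,000, no true effect, 400 runs per setting) gave spurious PRIME-minus-control differences of −0.5 to −4.7 points. With equal means it gave −0.09 to +0.05.

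**5. Scale.** With 70 per group and a two-sided 0.05 test, the difference detectable with 80% power is (1.960 + 0.842) × √(2/70) = 0.47 SD. The upper end of the assumed drift is close to that.

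**The case against.** The case on the other side is substantial, and much of it stands.

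- **The pool may not be unrestricted.** A reader might infer that controls of any age and risk are admitted. The article does not say so. It promises a comparable risk profile, and a fuller document may apply the criteria. What can be said is that the article does not state them for controls.
- **EuroSCORE II is a composite.** The matching sentence shares its reference with the Table 1 entries for obesity, mobility, reoperation and procedure weight, which suggests overlap with the PRIME criteria. This weakens the eligibility point but does not remove it, because equal totals can hide different components.
- **Diversion from surgery is not bias.** A reader might count PRIME patients moved to less invasive or conservative treatment as a distortion. If PRIME caused the move, it is part of the effect under study. Only the absence of controls declined or lost under usual care counts here. Even that is uncertain in size: some late reconsideration may fall after the control baseline, and patients who die have no one-year RAND-36 in either group.
- **Less post-operative time in PRIME is not shown.** A reader might infer that operated PRIME patients are measured sooner after surgery than controls. The control follow-up anchor and the interval from PRIME visit to surgery are not given.
- **Regression to the mean is not established.** It needs a healthier pool and an imperfect correlation. Matching also on EuroSCORE II would shrink the relevant gap if that score tracks RAND-36.
- **The comparison is secondary** in a study labelled exploratory and non-randomized.

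What remains is the unstated eligibility for controls, the different time zeros, and a claim of assured comparability that two matching variables cannot support.

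**Conclusion.** The point holds as a vulnerability in a secondary comparison. Followed as written, the control rule allows different eligibility and sets a different time zero in the two groups, and nothing in the article repairs this. Leaving out controls declined or lost before the pre-surgery window would plausibly favour controls, but its size cannot be derived.

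Regression to the mean would add to this only if the control pool has a higher mean RAND-36 than PRIME patients: about 0.09–0.40 SD under one assumed set of inputs, about 0.03–0.23 SD under another, and zero if the means are equal. The documents do not support saying that the comparison is biased by a known amount. The primary outcome, the change in Heart Team recommendation within PRIME patients, does not use the controls and is unaffected.

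**What to change.** 1. Before matching, restrict the pool to patients aged 70 or over with at least two Table 1 factors that can be scored from records.
2. Add age, and procedure class if available, to the matching or to a baseline-adjusted analysis.
3. Match within a caliper and report standardized differences, including for variables not matched on.
4. Where the database allows, use one index date in both groups (for example, the first Heart Team recommendation for surgery), include controls whether or not surgery followed, and run the same one-year clock. Section 2.8 already takes control age at Heart Team referral, so that date may be retrievable. State the control follow-up anchor in any case.
5. If the database holds only patients who reached surgery, label the comparison descriptive. Do not present contrasts of all PRIME patients and of operated PRIME patients against controls as bounds: eligibility differences and regression to the mean could push both the same way, so they need not bracket the truth.
6. In 2.3, say that matching is meant to improve comparability, not ensure it.

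The cost is a database filter and some wording. The downside is that fewer than 70 good matches may remain, with less precision. Restriction removes regression to the mean only as far as it brings the pool mean to the PRIME mean, so report both means.

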### 2.4. Recruitment

The Heart Team refers patients to the PRIME clinic for consultation if they meet the inclusion criteria. The patient will receive an invitation letter approximately 7–10 days prior to their scheduled visit to the outpatient clinic. This invitation includes a letter explaining the purpose of the PRIME clinic visit as well as information about the research being conducted. Patients who wish to participate in the study are requested in the letter to complete the enclosed informed consent form and bring it to their appointment at the PRIME clinic. A screening log is maintained to document the reasons why eligible patients do not participate despite meeting the inclusion criteria.

